## Abstract

**Background:**

Insomnia is often accompanied by depression and anxiety, which can seriously affect people’s quality of life. Cognitive behavioral therapy for insomnia (CBT-I) is the first-line treatment, but the existing CBT-I ignores the intervention for anxiety-depressive symptoms, and has poor efficacy due to the lack of artificial support, poor compliance, the inability to spread widely and high dropping rate. A balance is needed between the convenience and efficiency of web-based technology and patient needs. Again in this context, an online WeChat applet (Smart CBT-I plus) will be developed with CBT-I technology as the core, integrating cognitive behavioral intervention modules for depression and anxiety.

**Objectives:**

This study will validate the effectiveness and applicability of Smart CBT-I plus by examining whether the Smart CBT-I plus study group will significantly reduce the distress of people suffering from insomnia with anxiety and/or depression symptoms compared to the psychoeducational group.

**Methods:**

In this parallel-group, randomized controlled trial, 180 patients seeking help for insomnia combined with anxiety and/or depression will be recruited, and they will be randomized with 60 patients being assigned to the psychoeducation group (control group), and 120 patients being assigned to the Smart CBT-I plus group (study group). Measurements will be taken at baseline, post-intervention, 6 and 12 month follow-up, at the same time, semi-structured qualitative interviews about the experience of using Smart CBT-I plus will be conducted with randomly selected patients from the study group.

**Results:**

The results will involve insomnia, depression and anxiety to explore its effectiveness, in-treatment dropout rates and subjective patient feedback to explore the applicability of Smart CBT-I plus.

**Future recommendations:**

Self-help platforms need to be more individually designed to reach a wider audience. Research aimed at a wider audience, such as the general public, will make the research more universal and the platform more meaningful.

## Introduction

1

### Background

1.1

Insomnia is a serious public health problem, 19% to 50% of adults report experiencing insomnia, and approximately 10% meeting the diagnostic criteria for insomnia disorders (1, 2). Insomnia seriously affects the quality and efficiency of life and is one of the causes of many psychiatric disorders, such as anxiety and depression (3, 4).

For a long time, medication has dominated the treatment of insomnia but they are difficult to cure insomnia and have many side effects (5–7).Cognitive Behavioral Treatment of Insomnia (CBT-I) is a psychotherapy that addresses maladaptive behaviors and the dysfunctional concepts that perpetuate sleep problems, and is effective in improving sleep when treated in person by a trained therapist (8, 9). Studies have shown that the short-term effects of CBT-I are comparable to medication (9), while long-term efficacy is superior to medication (10). Several meta-analyses in recent years have shown that CBT-I is effective in different types of insomnia, including primary insomnia versus co-morbid insomnia (11), middle-aged and older adults (12, 13) and children and adolescents (14, 15).

In an early study investigating the relationship between insomnia and mental illness, 40% of them suffered from psychiatric disorder, most commonly anxiety (24%) or depression (14%) (3, 16, 17). Insomnia is closely related to anxiety and/or depression (18–20), and they have a mutually sustaining relationship (20–22). This suggests that improving concomitant anxiety and depressive symptoms in insomniac subjects is clinically important (23).

CBT-I has been gradually and widely used in the treatment of insomnia, but it has strong limitations, which are mainly reflected in the poor durability and stability of the efficacy, and the high relapse rate (24–26). Offline face-to-face CBT-I focuses on the treatment of “insomnia” itself, but neglecting the impact of negative emotions such as anxiety and depression on sleep. As offline face-to-face CBT-I is difficult to be widely promoted in practice due to problems such as expensive, time-consuming and lack of professional therapists (27), online or non-online self-help CBT-I, which helps patients achieve self-help treatments with the help of carriers such as books, computers, and mini-palm devices, has gradually appeared and has been proved to have a certain degree of efficacy (20, 28). However, they can also be undermined by a lack of professional guidance and the patient’s difficulty in accurately understanding the key points of the treatment.

Online self-help CBT-I programs relying on the Internet make it easier for users to receive different forms of information at the same time, have a higher degree of interactivity than non-online self-help CBT-I programs, and are able to provide more timely feedback (20). In contrast, online self-help CBT-I treatments in which some support is given to the patient through email, phone calls, etc., have a significant impact on its efficacy, which may help to increase adherence to the treatment, reduce the rate of disengagement, and thus promote efficacy (29). Therefore, online self-help CBT-I programs with a certain degree of interactivity and therapist support will have greater application value.

In this study, we developed a CBT-I based online intensive cognitive behavioral therapy for insomnia combined with anxiety and depression applet for patients with insomnia combined with anxiety and depression, which is a personalized online self-help CBT-I program for people with insomnia combined with anxiety and depressive symptoms. As mentioned above, because it is of great significance to improve the anxiety and depression symptoms associated with insomnia patients, the program developed in this study not only arranges the content of CBT-I, but also specially adds the treatment module for anxiety and depression, it’s called Smart CBT-I plus. Because Smart CBT-I plus intervention needs to be completed in a continuous 35 days, and the addition of the anxiety and depression module of the intervention is also a strengthening of the efficacy, it is therefore an intensive intervention. After the daily interventions targeting sleep disorders are completed, the program automatically reminds the patient to use the intervention modules for anxiety and depression. I call it Online Intensive Cognitive Behavioral Therapy for Insomnia (Smart CBT-I plus). Smart CBT-I plus is an online WeChat applet with human-computer interaction functions. When patients have doubts about the treatment content or need human intervention, they can go to the therapist’s mailbox on the homepage to give feedback, and the therapist will tailor the treatment to the patient’s needs and provide the necessary human support. CBT-I This study attempts to evaluate the effectiveness and applicability of Smart CBT-I plus.

### Objectives

1.2

This study will conduct a prospective, parallel-group, randomized controlled clinical trial to investigate the effectiveness of Smart CBT-I plus in improving symptoms in patients with insomnia with anxiety and depression and the applicability, strengths and weaknesses, and directions for refinement of the procedure itself.

## Methods

2

### Trial design

2.1

This will be a single-center, parallel group, randomized controlled trial. A total of 180 patients with insomnia disorder combined with anxiety and/or depressive symptoms will be recruited and randomly assigned in a ratio of 1:2 to the online psychoeducation group (control group) and the Smart CBT-I plus treatment group (study group), and followed up at 6 months, and 12 months after the treatment. Both the control and study groups will be done online.

### Setting and recruitment

2.2

We will enroll patients with insomnia with anxiety and/or depression symptoms in outpatient and inpatient clinics of Shanghai Mental Health Centre through poster publicity, online recruitment, and doctor recommendation. Patients who meet DSM-5 diagnostic criteria for insomnia and have comorbid psychological disorders will be recruited and referred by psychiatrists and psychotherapists with medical backgrounds at the Shanghai Mental Health Center, and then assessed by trained assessors.Patients who meet the inclusion criteria and sign the electronic informed consent forms (ICFs) will be randomly assigned to the control group and the study group, and the randomization will be confidential to the assessors. Next, a systematic semi-structured sleep assessment interview will be conducted by a professional psychotherapist who has undergone uniform training to assess the patient’s insomnia severity, social functioning, and basic upbringing history, to complete the conceptualization of the case of insomnia, to establish a preliminary therapeutic relationship, and to provide an introduction to the upcoming online intervention, which will last for approximately 1 hour. During this process, if the subject does not feel comfortable or has difficulty cooperating with the treatment, or if the therapist believes that the treatment program is not suitable for the subject, then the therapist will not enroll him/her in the group. The Insomnia Severity Index (ISI), Hamilton Depression Scale (HAMD) and Hamilton Anxiety Scale (HAMA) will be used for screening. Other criteria are listed in the “participants and eligibility” section. Participants who meet the criteria will be able to proceed to the next stage. The specific flowchart is found in **Figure 1**.

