### Randomization

2.4

Randomization will be based on a computer-generated list of random numbers randomly assigned in a 1:2 ratio to the online psychoeducational group (control group) and the online Smart CBT-I plus group (study group). Later, the computer program will use the generated random list to allocate patients, and the research assistant will inform the trained psychotherapist of the results of the randomized group of patients after allocation, and after the therapist’s interviews, allocate them to the corresponding control and intervention group fellows.

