### Participant timeline

2.6

At baseline and at the end of the intervention, patients will be subjected to a series of psychological assessments, including sleep and mood symptoms. For patients in the study group, at the end of the 35-day intervention, a random sample of 30 patients will also be given a one-on-one qualitative interview to discuss their experience with Smart CBT-I plus, the interview results will be recorded. All patients will be evaluated at follow-up at 6 and 12 months after completion of treatment. Patients will be made aware of all assessment results. They will also be able to view their weekly assessments on their own in the program. they will still be able to use the program on their own after the 35-day session. The specific follow-up schedule is shown in **Table 1**.

**Table 1 T1:** Subject visit schedule.

items	Screening visit	Baseline visit	Post-intervention visit	Follow-up visit	
Visit	V0	V1	V2	V3	V4
Time	Day -7-0 * (± 1 day)	Day 0 (± 1 day)	35 days after baseline (± 3 days)	6 months after intervention (± 7 days)	12 months after intervention (± 7 days)
Sign informed consent	**×**				
Inclusion/exclusion criteria	**×**	**×**			
Self-made general demographic questionnaire		**×**			
Self-made clinical feature collection scale		**×**			
Semi-structured sleep assessment questionnaire		**×**			
Insomnia Severity Index Scale (ISI)	**×**	**×**	**×**	**×**	**×**
Hamilton Depression Scale (HAMD)	**×**	**×**	**×**	**×**	**×**
Hamilton Anxiety Scale (HAMA)	**×**	**×**	**×**	**×**	**×**
Clinical Gross Impression Scale (CGI)		**×**	**×**	**×**	**×**
Epworth Sleepiness Scale (ESS)		**×**	**×**	**×**	**×**
Pittsburgh Sleep Quality Index Scale (PSQI)		**×**	**×**	**×**	**×**
Hygiene economics evaluation		**×**	**×**	**×**	**×**
Adverse event report form			**×**	**×**	**×**
Serious Adverse Event (SAE) report form			**×**	**×**	**×**
Six quality of life questionnaires		**×**	**×**	**×**	**×**
Generalized Anxiety Scale (GAD-7)		**×**	**×**	**×**	**×**
Dysfunctional Beliefs and Attitudes about Sleep Scale (DBAS-16)		**×**	**×**	**×**	**×**
Rapid Report of Depressive Symptoms - Self-report score 16 items (QIDS-SR16)		**×**	**×**	**×**	**×**
Life Event Scale (LES)		**×**			
Therapeutic Alliance Questionnaire Revision (WAI-S)			** *×* **		
Outline of semi-structured qualitative interviews (30 patients of study group)			** *×* **		
medication administration record	**×**	**×**	**×**	**×**	**×**

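### Sections 2.2 and 2.4 do not agree with Table 1 on where randomisation falls relative to V1, so self-rated baselines can be taken after allocation and after the therapist interview

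*Protocol article*

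**What the plan says.** **Order of steps.** Section 2.2 (Setting and recruitment) says that patients who meet the criteria and have consented "will be randomly assigned to the control group and the study group, and the randomization will be confidential to the assessors". The following sentence begins: "Next, a systematic semi-structured sleep assessment interview will be conducted by a professional psychotherapist who has undergone uniform training". Among the purposes of that interview are "to establish a preliminary therapeutic relationship, and to provide an introduction to the upcoming online intervention".

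**Who knows the arm.** Section 2.4 (Randomization) says that "the research assistant will inform the trained psychotherapist of the results of the randomized group of patients after allocation, and after the therapist’s interviews" the patients pass to their group. So the therapist is told the result once allocation is made, and formal placement in the group waits until the interview is over.

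**Visits.** Table 1 (section 2.6) ticks the row "Semi-structured sleep assessment questionnaire" at V1 only, the baseline visit on Day 0. The ISI is ticked at V0 (screening), V1 and every later visit, as are HAMD and HAMA. PSQI, DBAS-16, GAD-7 and QIDS-SR16 are first ticked at V1. The row "Inclusion/exclusion criteria" is ticked at both V0 and V1. The table has no row for randomisation.

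**Use of the baseline.** Section 3 describes the ISI as a self-assessment tool and names two main indicators: ISI compared between groups after the intervention, and ISI compared within group before and after. Success is tied to the between-group difference after 35 days. Most secondary indicators are changes or reduction rates. Section 4 plans t-tests and repeated-measures ANOVA with a group × time interaction.

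**The concern.** A baseline serves as a reference for change only if allocation cannot have influenced it. On the sequence in sections 2.2 and 2.4, the interview comes after randomisation and is held by a therapist who knows the arm. It also introduces what the patient is about to receive: the applet, or one article a day. Table 1 places that interview in the same visit as the baseline questionnaires.

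A patient who fills in the ISI or PSQI after such an hour may rate it differently according to arm, from hope in one group or disappointment in the other. Keeping the allocation from the assessors does not help with scales that patients complete themselves. An arm difference created at V1 would pass into every quantity that subtracts or divides by the V1 value. It could not be repaired later for scales that have no earlier measurement.

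**Working it through.** The plan gives no figure on this point, so the main check sets the passages side by side.

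| Place | What it implies for randomisation |
|---|---|
| Section 2.2, consent and criteria met, then random assignment, then the interview | before the interview |
| Section 2.4, therapist told the result, interview, then placement in the group | before the interview |
| Table 1, interview at V1 only | with the two rows above: before or during V1 |
| Table 1, eligibility checked again at V1 | fits randomisation at the end of V1 or later |
| Section 2.2, therapist may still decline to enrol after the interview | fits randomisation after the interview |

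The first three rows put randomisation before the V1 interview. The last two fit a later position. No sentence fixes the order of questionnaires and interview within V1, or places the questionnaires ahead of randomisation.

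**Which measures have a value before V1 (Table 1).** ISI, HAMD and HAMA: yes, at V0. PSQI, DBAS-16, GAD-7 and QIDS-SR16: no.

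**Which analyses use the baseline (sections 3 and 4).**
- Between-group ISI at day 35: no.
- Within-group before/after ISI: yes.
- Group × time interaction: yes.
- Reduction rate in PSQI, and change in PSQI factors, DBAS-16, sleep latency and total sleep time: yes.
- Reduction rates in HAMA and HAMD: yes, though these are less exposed to the self-rating route to the extent that a blinded assessor does the rating.

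**Illustration of size.** The only input from the documents is the effect size of 0.5 (section 2.7). The ISI SD of 5 and the size of the shift are assumptions. Let s be the study-minus-control difference in V1 ISI caused by the arm being known, and let the true effect be −0.5 SD (lower is better).

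- Post-only contrast = −0.5 SD, whatever s is.
- Change contrast = −0.5 − s, in SD units. This is also the group × time contrast of V1 against a later visit.

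| s (SD) | s in points (SD 5) | change contrast (SD) | change contrast in points |
|---|---|---|---|
| −0.2 | −1.0 | −0.3 | −1.5 |
| −0.1 | −0.5 | −0.4 | −2.0 |
| +0.1 | +0.5 | −0.6 | −3.0 |
| +0.2 | +1.0 | −0.7 | −3.5 |

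The target is 0.5 × 5 = 2.5 points. A 1-point shift is 1/2.5 = 40% of it, in either direction. Section 4 names no baseline-adjusted model, so none is illustrated.

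**The case against.** The strongest reply is that the harm needs two steps the article does not state.

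1. **The patient must know the arm when rating V1.** Section 2.4 says the therapist is informed. It does not say when the patient is. Both arms are delivered online, so introducing the upcoming online intervention does not by itself show that the arm is disclosed.
2. **The questionnaires must follow the interview.** Table 1 lists visits, not the order within a visit.

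Both limits stand. A reader might infer that the baseline ISI is certainly collected unblinded after allocation; the documents show only that the stated sequence allows it.

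It can also be said that order within a visit is detail an article may leave to the full protocol, and that Figure 1, which is not shown here, may settle it. That weakens any complaint of omission. It does not remove the disagreement between what sections 2.2 and 2.4 do say and what Table 1 shows. Section 2.2 is also a loose timeline: it mentions screening scales after the interview, although randomisation has already been described. That supports calling the position of randomisation unclear, and it is a further reason to reconcile the text.

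Two stronger readings should be resisted.

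- **That the primary test is biased.** The success criterion is a between-group comparison of ISI at day 35 and does not subtract baseline. Section 4 does exclude cases without a baseline value of the primary indicator, which might suggest an indirect route. But the article does not say that this baseline is the V1 value rather than V0, or that missing values would differ by arm.
- **That baseline-adjusted estimates are affected.** No such analysis is planned in the document.

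**Conclusion.** The point holds as an inconsistency with a plausible route to bias, not as a demonstrated bias. Sections 2.2 and 2.4 put allocation before the interview, Table 1 puts the interview in the baseline visit, and the repeated eligibility check and the late option not to enrol point the other way. If the stated sequence is followed, the self-rated V1 values can be taken after allocation and after the interview.

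Exposed are the before/after ISI comparison, the group × time analysis and the change or reduction-rate outcomes for PSQI, DBAS-16, sleep latency and total sleep time. The article does not say which instrument supplies the last two; they are exposed in so far as their starting value is reported at V1.

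No actual size can be derived from the documents. The 1 point against a target of 2.5 rests on an assumed SD of 5 and an assumed shift, and only shows that a modest distortion would matter for a change contrast. The point deserves correction because the remedy is nearly free and the damage could not be undone for scales first measured at V1.

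**What to change.** Reconcile sections 2.2 and 2.4 with Table 1:

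- State that all V1 scales are completed before the allocation is generated or disclosed, and before the therapist interview.
- Add a randomisation row to Table 1, placed after the V1 scales.
- State whether the V1 eligibility check and the therapist's decision not to enrol come before or after randomisation, so that text and table give one sequence.

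This re-orders steps around one visit and adds no assessment.

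If V1 cannot precede allocation, name V0 as the analysis baseline for ISI, HAMD and HAMA. This fallback is only partial: PSQI, DBAS-16, GAD-7 and QIDS-SR16 have no V0 value and would stay unprotected. Re-ordering should therefore be the main remedy.

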## Statistical analysis

4

The datasets included in the statistical analyses will be divided into the Full analysis set (FAS) and the Per Protocol Set (PPS). FAS refers to people who have had at least one follow-up after enrollment and have data on key indicators. Cases missing baseline data for the primary evaluation indicator will be excluded. PPS refers to cases that meet the inclusion and exclusion criteria on the basis of FAS, have valid baseline values, have good adherence, and do not violate the clinical study protocol. Data will be analyzed using both the FAS and the PPS, with FAS results being the mainstay.

Statistical tests will be performed using SPSS version 23.0 software and relevant data will be considered statistically significant if P < 0.05. Comparisons between groups will be made using chi-square analysis, continuous variables will be statistically described using mean ± standard deviation (M ± SD), comparisons between the two groups will be made using the independent samples t-test, and repeated measures such as ANOVA will also be used to compare the degree of symptomatic improvement in the intervention group and the control group and to analyze the group × time interaction. In addition, Binary Logistics regression and COX regression will be used to compare the changes in each indicator before and after the intervention between the two groups. Multiple imputation will be used for handling missing data.

Data will be analyzed using content analysis to extract patients’ experiences of using the Smart CBT-I plus. The audio recordings of the semi-sectional constructed interviews will be transcribed into text before the interview data is independently coded and analyzed by each of the 2 researchers, and if inconsistencies are encountered, they will be discussed to reach consistent conclusions, and inter-researcher coding consistency will be used to rate the study’s reliability.

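### As written, a therapist who knows the arm may decline to enrol patients after randomisation, and the main analysis set then leaves those patients out

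*Protocol article*

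**What the plan says.** Under Setting and recruitment (2.2), patients who meet the inclusion criteria and sign consent "will be randomly assigned to the control group and the study group, and the randomization will be confidential to the assessors". The next sentence reads "Next, a systematic semi-structured sleep assessment interview will be conducted by a professional psychotherapist". The interview lasts about an hour, assesses the patient and introduces the coming online intervention. Two things at this interview can end a patient's participation. One is on the patient's side: "if the subject does not feel comfortable or has difficulty cooperating with the treatment". The other is the therapist's judgement: "if the therapist believes that the treatment program is not suitable for the subject, then the therapist will not enroll him/her in the group". No objective criterion is given for either.

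The Randomization section (2.4) says who knows the arm. After the list has been applied, "the research assistant will inform the trained psychotherapist of the results of the randomized group of patients after allocation". Only after the therapist's interviews does the section "allocate them to the corresponding control and intervention group fellows".

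The Statistical analysis section (4) makes the full analysis set the main one and defines it so: "FAS refers to people who have had at least one follow-up after enrollment and have data on key indicators".

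**The concern.** Randomisation makes the arms comparable only for the people who were randomised. Here a discretionary exclusion comes after allocation, and the person who makes it knows the arm. Concealment from the assessors (2.2) and an unaware statistician (section 3) do not touch this step, because the gatekeeper is the therapist.

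Refusal could well differ by arm. Suitability is judged against a programme, and the programmes are unlike each other. The study arm has 35 days of daily applet tasks that include sleep restriction; the control arm gets one article a day and a one-word reply. The Discussion itself expects the applet to suit patients who are more adherent and engaged, and an hour's interview is likely to pick up those traits.

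At stake are the primary ISI comparison and two applicability measures, all-cause dropout and completion. Removing likely non-completers before they count as enrolled would make both of those look better.

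**Working it through.** **Sequence.** Setting 2.2, 2.4 and 4 side by side gives this order:

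1. Eligibility and consent (2.2).
2. Random assignment, hidden from the assessors (2.2).
3. The therapist is told the arm (2.4).
4. Interview, with the option not to enrol (2.2).
5. Placement in the arm (2.4).
6. Full analysis set: at least one follow-up after enrolment, with data on key indicators (4).

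The order does not hang on one loose connecting word in 2.2, because 2.4 independently puts disclosure after allocation and placement after the interview. A patient stopped at step 4 never reaches step 6. The multiple imputation planned in section 4 does not bring that patient back, since as defined the patient is outside the set being imputed.

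**Plan's own figure.** The protocol gives no refusal rate and no allowance for refusals, so there is nothing to reproduce on this point. The calculation below is an illustration.

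**Inputs from the protocol (2.7).** 60 control and 120 study patients, 15% dropout, standardised effect 0.5, significance level 0.05. Sidedness is not stated; I take it as two-sided. Analysed: 60 × 0.85 = 51 and 120 × 0.85 = 102.

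**Assumed inputs (not in the protocol).** A fraction q of 5% to 15% of the study arm is refused and nobody in the control arm. Those refused would have ended g = 0.5 to 1 SD worse on the ISI than those kept. There is no true effect.

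**Bias.** The mean of those kept differs from the mean of everyone randomised to that arm by b = q × g.

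- Low end: 0.05 × 0.5 = 0.025 SD, or 0.025 / 0.5 = 5% of the planned effect.
- High end: 0.15 × 1 = 0.15 SD, or 0.15 / 0.5 = 30% of the planned effect.

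**Type I error.** The test statistic is shifted by b × √(51 × 102 / 153) = b × √34 = 5.83b. The two-sided error is P(Z > 1.96 − 5.83b) + P(Z < −1.96 − 5.83b).

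| b (SD) | shift | two-sided type I error |
|---|---|---|
| 0.025 | 0.146 | 5.2% |
| 0.05 | 0.292 | 6.0% |
| 0.10 | 0.583 | 9.0% |
| 0.15 | 0.875 | 14.1% |

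If the 15% refused come off the study arm on top of dropout, 120 × 0.85 × 0.85 = 86.7 are analysed there. The last row then becomes 13.6%, so this detail hardly matters.

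**Second model.** Suppose the study-arm patients with the worst perceived prognosis are refused, perceived prognosis correlates 0.5 with outcome, and 60 and 120 are randomised. Refusing 5%, 10% and 15% gives a bias of 0.05, 0.10 and 0.14 SD and a type I error of 6.6%, 9.8% and 14.3%. A simulation of the 10% case gave 10.0%. With a correlation of 0.3 the three error rates are 5.5%, 6.6% and 8.1%. With a correlation of 1.0 they are 12.1%, 27.9% and 48.4%, but that supposes a therapist who predicts outcome perfectly.

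**Refusals in both arms.** In general b = (q × g in the study arm) − (q × g in the control arm). With g = 1 SD throughout, 10% refused in the study arm and 5% in the control arm gives 0.10 − 0.05 = 0.05 SD. Equal rates give zero. Refusals in the control arm alone reverse the sign.

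**The case against.** The strongest reply is that section 2.2 is not strictly chronological. It mentions the screening scales, and patients proceeding to the next stage, after the interview, although screening must come before assignment. Exclusion criteria 10 and 11 in section 2.3 overlap with the interview refusal, and Table 1 puts the interview at V1 beside the eligibility check. The interview may therefore be meant as the last eligibility step. Figure 1 is not available here and Table 1 has no randomisation row, so neither settles the order. What stands is that the intention may be sound; but 2.4 says the therapist learns the arm after allocation and places patients after the interview, and nothing overrides that. The finding is about the plan as written.

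The second reply is that the size and direction of the bias are assumed. That is correct. Control patients might also leave at the interview, for example on learning that they will only receive articles.

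A reader might also infer that baseline scores are taken once the arm is known, because the interview and the baseline scales share the V1 column. The document does not support this. Table 1 gives no order within V1; ISI, HAMD and HAMA are also taken at the V0 screening visit; and the assessors are kept unaware of the allocation.

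Last, the interview also introduces the intervention and builds a therapeutic relationship, so moving it as a whole may not be practical. That stands, and the fix allows for it.

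**Conclusion.** The concern holds for the text as written. Arm-aware, discretionary refusal after randomisation, together with an analysis set conditional on enrolment, leaves the primary comparison and the dropout and completion measures open to selection bias. Because the fix is cheap and the primary result is exposed, it should be made before recruitment goes further.

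The size is unknown. Under refusals of 5% to 15% in the study arm only and an outcome gap of 0.5 to 1 SD, the bias is 0.025 to 0.15 SD in the applet's favour and the two-sided type I error about 5% to 14%. Refusals in the control arm would shrink, cancel or reverse it.

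Two stronger conclusions are tempting and not supported. One is that the comparison is biased: it could be, if refusals differ by arm in a way related to outcome. The other is that no later analysis could repair the damage: if refused patients are followed up and analysed in their randomised arm, this step introduces no bias. The loss becomes irreparable only if they are not followed.

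**What to change.** - Complete the suitability part of the interview and the enrolment decision before randomisation. Alternatively, keep the therapist blind to the arm until enrolment is confirmed. Leave any arm-specific introduction until after allocation.
- Define the main analysis set as all randomised patients, in the arm to which they were randomised.
- Follow up anyone who does not start the programme after randomisation, and report these cases by arm with reasons. This concerns follow-up and analysis only; whether a given patient starts a programme remains a clinical decision.
- Bring sections 2.2 and 2.4 into line, so that both give the same order of interview, allocation and disclosure.

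Cost: a wording change and a reordering of existing steps. The interview may need to be split in two, some interviews will be spent on people who are never randomised, and the few who are randomised but do not start will need follow-up.
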